### The roles of stakeholders of the research

The university researchers on the team are also experienced clinical psychologists working with young people (AE and MC). The University of Paris Cité is an institutional partner in the study. The partner organizations in the research project will contribute by disseminating the cross-sectional study online at the regional and national levels. The MLs in Paris are also contributing by offering services (food assistance, psychotherapist interventions) that we are using and adapting for the study.

The social work teams within each organization will facilitate the communication of information about the different phases of the study, invite the young people they support to participate, and host meetings with participants at their facilities. The scientific director of this research, AE, assumes overall responsibility for the project, including budget oversight and adherence to ethical procedures.

### Ethical considerations

We obtained approval from the Committee for the Protection of Persons (CPP) Ile de France XI to conduct this study, classified as a Minimal Risk Interventional Research (RIPH 2) study, and registered under number ID-RCB: 2025-A01928-41.

In addition, the MISAPSY project received a favorable opinion from the Ethics Committee (EC) of the Hôpitaux de Saint-Maurice (PR-2024-6) and the EC of the University of Lorraine (AE2025-0037). The research project is also registered in the data processing registry of the University of Lorraine under number 2025 − 462 and adheres to the Reference Methodology MR-001, French regulations defined by the National Commission for Information Technology and Civil Liberties (CNIL) govern research involving personal data in the health sector. In accordance with the General Data Protection Regulation (GDPR) and the University of Lorraine’s internal guidelines, these records ensure that the processing of participants’ personal data complies with ethical and legal data protection standards.

Any information that could identify participants will be removed before data analysis to guarantee their anonymity.

### Data monitoring and management

As data monitoring responsibilities are shared among the research team members, no data monitoring committee has been appointed. Data entry will be verified twice to ensure accuracy, and data quality will be assured through range checks. Participants will receive reminders. If they do not attend the appointments (study 3), reminders will be sent by text message or email. Data already collected from participants who have ended their participation will be retained for analysis. All data will be pseudonymized via a lookup table during the active phase of the study. After this, the lookup table will be destroyed to render the data completely anonymous. Considering the minimal-risk nature of the study, it will only be discontinued prematurely in case of unforeseen ethical concerns.

### Safety considerations

The instruments used in this study are standardized and validated questionnaires. They have been widely used in previous studies involving young and vulnerable populations, often through self-administration. Their use does not present any specific identified risks, apart from possible occasional discomfort when reflecting on certain personal situations.

Regarding the qualitative interviews in Study 2, no adverse effects are expected. However, the semi-structured interviews in Study 3 comprise a period for gathering information and subjective experiences, particularly during the initial meeting. Although conducted in a respectful and non-intrusive manner, these exchanges may potentially elicit emotions related to past or present events, especially in the context of a history of precarious living conditions, family instability, or childhood adversity.

To mitigate this risk, all interviews will be conducted by experienced psychologists trained in trauma clinical practice and in gathering information in vulnerable situations. In cases of obvious distress or a perceived need for more specific support, participants can be immediately referred to the psychologists at the ML.

If a psychiatric evaluation is deemed necessary a referral to a partner psychiatrist can be made. These resources are available regardless of the participant’s assigned group.

All of these measures help minimize potential psychological risks and ensure rapid and appropriate support when needed. If an exclusion criterion is met during the study, participation will be stopped.

Withdrawal of participants is entirely voluntary and will have no consequences, thus ensuring adherence to ethical research principles. Withdrawal of consent during data collection constitutes termination of participation. Participants who cease participating in research interviews or discontinue their participation in the support program will be considered lost to follow-up.

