Type of study Method	Quantitative Cross-sectional study using self-administered questionnaires	Qualitative Semi-structured interviews	Longitudinal Intervention programs Self-administered questionnaires and semi-structured interviews
Eligibility criteria	Participant aged 18–25 Currently being supported by the Mission Locale	Being a psychologist Currently working at the Mission Locale Have at least one young adult in their active caseload	Participant aged 18–25 Currently enrolled in an insertion program in the Mission Locale Answer “yes” at item 8 of the FIES PHQ-9 score > 15 GAD-7 score > 10 exposed to one or more ACEs (CTQ-SF)
Exclusion criteria	Minors Do not speak and read French Under Guardianship or Curatorship Unable to provide informed consent	Not having psychological follow-up at the Mission Locale Unable to provide informed consent	Minors Do not speak and read French Under Guardianship or Curatorship Unable to provide informed consent Currently receiving psychiatric care for an acute or chronic mental illness requiring regular specialized treatment Presenting a social or medical emergency situation incompatible with the study Having already participated in a similar study or being currently engaged in a structured psychological intervention protocol
Main Outcomes	Food Insecurity prevalence Mental health aspects (anxiety, depression, PTSD and CPTSD) Childhood trauma Psychological resources (defense mechanisms, resilience, perceived social support) Substances use Quality of sleep	Psychological practice and working conditions Organization of care Perspective on the young people encountered Sensitivity to issues of trauma and vulnerability	Childhood trauma Mental health aspects (anxiety, depression, PTSD and CPTSD) Food Insecurity level Defense mechanisms Anamnesis, current living conditions, adherence and perception of interventions
Analysis	Quantitative analysis	Thematic analysis	Quantitative and qualitative analysis

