Recruitment: The longitudinal study is intended for young people from MLP. Young people will be recruited through an explanatory email and the distribution of a flyer in the 6 MLP. Young people who have expressed interest will be interviewed by a member of the research team to verify their eligibility (see: Table 1), provide them with a detailed information sheet (see: supplementary material), and answer any questions. Eligible persons will then have 15 days to consider their decision and formalize their participation by signing the informed consent form (see: supplementary material).Randomization procedure: Participants will be assigned to one of two arms using a single-blind randomization procedure (1:1 allocation ratio). The assignment will be handled by a researcher who will not perform the data analysis, using a computer and a random number generator. The sequence will be stored in a secure file until participant enrollment is completed. Due to the nature of the intervention, neither the participants nor the facilitators (partner psychologists) can be blinded to group membership. However, the analysts of the outcome data will remain blinded to this group membership during statistical analyses. No formal unblinding procedure is planned, as there is no blinding at the participant level.Intervention and comparator: The control group will receive food assistance once a week for 12 months. The experimental group will receive the same food aid and in addition, psychological support twice a month for 6 months. The psychological support consists of individual sessions conducted by experienced psychodynamic psychologists and partners of the MLP. Food aid consists of distributing food baskets from MLP partner associations. The services are already offered by the MLP and are simply being reorganized within the framework of the study. In order not to deprive participants of potential care, the comparison of these two distinct approaches was guided by strong ethical considerations.Assessments and outcomes: These conditions enable the effects of different types of interventions to be measured within a supportive framework. Each participant will have 4 evaluation times during the year (T0, T1, T2, T3). Each time, they will first complete standardized scales and then have a semi-structured interview (see: Fig. 1). The interview will aim to characterize the participant’s experience, gather information about their history (T0), and assess their adherence to the proposed follow-up care, living conditions, interpersonal relationships, and future projections (T1, T2, T3). A closing session (T3) will also allow for a retrospective evaluation of the experience of the program, the maintenance of its effects, and the desire to continue the follow-up care. The primary outcome is the change in food insecurity level between baseline (T0) to 12 months (T3). Secondary outcomes include: (1) change in depressive symptoms (PHQ-9 score), change in anxiety symptoms (GAD-7 score), change in PTSD and CPTSD symptom dimensions (ITQ criteria) and change in defensive functioning (DSQ-40 scores). Adherence to food assistance and/or psychological support and any change in participant situation will be documented based on self-report during semi-structured interviews.

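### Leaving the support programme, or meeting an exclusion criterion after randomisation, appears to end outcome collection; the resulting missing data can bias the randomised comparison in either direction

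*Protocol article*

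**What the plan says.** Study 3 randomises 70 people 1:1. The programmes differ by one component (Procedures, Study 3). Controls get weekly food aid for a year. For the other arm the text reads: "The experimental group will receive the same food aid and in addition, psychological support twice a month for 6 months". The primary outcome is the change in food insecurity from T0 to T3, at 12 months. Depression, anxiety, trauma symptoms and defensive functioning are secondary.

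Two sentences under Safety considerations govern what happens after entry:
- "Participants who cease participating in research interviews or discontinue their participation in the support program will be considered lost to follow-up".
- "If an exclusion criterion is met during the study, participation will be stopped".

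The Study 3 exclusion criteria in Table 1 include "Currently receiving psychiatric care for an acute or chronic mental illness requiring regular specialized treatment" and "Presenting a social or medical emergency situation incompatible with the study". Safety considerations also provides, in both arms, for referral to psychologists and, where needed, to psychiatry: "If a psychiatric evaluation is deemed necessary a referral to a partner psychiatrist can be made".

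Three other places bear on the point:
- Data monitoring and management keeps what was collected before a participant ended participation, and sends reminders for missed Study 3 appointments.
- Procedures, Study 3, records adherence to food aid and psychological support by self-report in the interviews, with adherence an interview topic at T1, T2 and T3.
- Data analysis, Study 3, plans a linear mixed model, with multiple imputation as an option above 5% missing.

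Nothing shown provides for assessing someone after they leave the programme or after participation is stopped.

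**The concern.** Stopping a support programme and stopping outcome assessment are different events. The first sentence gives them the same status, so a participant who leaves the programme but would still answer the scales is classed with those who cannot be reached. The second sentence ends participation on events that can follow a worsening after randomisation.

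Both rules therefore create missing outcomes after randomisation that need not be missing, and the missingness can be informative in two ways:

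- **By arm.** The experimental programme has an extra component that can be discontinued. If dropping only that component counts as discontinuing the programme, the rule acts more often in that arm.
- **By outcome.** A worsening between visits can lead to regular psychiatric care, or appear as a social emergency, and stop participation before the worsening is measured.

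At stake is whether the T3 contrast still compares the groups as randomised. An analysis plan cannot settle this later, because it cannot recover outcomes that were never collected.

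**Working it through.** **1. Is there a figure to reproduce?** No. Participants, Study 3, gives 70 (35 per arm) on pragmatic grounds, with no power, effect size, SD or dropout input. All dropout rates, shifts and correlations below are assumptions.

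**2. The passages side by side.** The adherence interviews at T1 to T3 imply that people who adhere poorly are still seen. The loss-to-follow-up sentence implies that people who leave the programme are not. The referral paragraph leaves a route to psychiatric care open in both arms, while the stopping sentence ends participation once such care is regular. The text does not say whether stopped participation means the support, the assessments or both.

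**3. Bias when stoppers worsen after their last visit.** Let pE and pC be the proportions stopping in the experimental and control arms. Let D be how much worse stoppers end up, in SD, than their observed scores predict, taken as equal in both arms. A missing-at-random analysis fills in the prediction and misses D, so

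bias in the T3 difference = (pE − pC) × D.

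- 30% v 10%, D = 0.5: 0.20 × 0.5 = 0.10 SD in favour of the experimental arm.
- 30% v 10%, D = 1.0: 0.20 × 1.0 = 0.20 SD in favour of the experimental arm.
- 10% v 30%: the same sizes, against the experimental arm.
- Equal proportions: zero.

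A large-sample simulation (four visits, common correlation 0.5, dropout after T1, prediction from T0 and T1) returned 0.10, 0.15 and 0.20 SD for D = 0.5, 0.75 and 1.0.

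**4. A second mechanism, without a fixed D.** Four visits, serial correlation 0.6, no true effect, 100,000 per arm. At each visit, stopping falls on those with the worst scores: either the last observed score or the current unobserved one. The analysis is a likelihood estimate with unstructured covariance. Higher scores are worse, so a negative bias favours the experimental arm.

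| Missing at T3, control v experimental | Stopping depends on last observed score | Stopping depends on current unobserved score |
|---|---|---|
| 0% v 24% | −0.01 SD | −0.19 SD |
| 8% v 24% | 0.00 SD | −0.12 SD |
| 13% v 34% | 0.00 SD | −0.14 SD |
| 13% v 13% | 0.00 SD | 0.00 SD |
| 24% v 8% | 0.00 SD | +0.11 SD |

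**5. What the first scenario does to error rates.** With 30% v 10% stopping, 35 × 0.7 = 24.5 and 35 × 0.9 = 31.5 remain, taken as 25 and 31. SE = √(1/25 + 1/31) = 0.269 SD. With no true effect, the chance of declaring benefit is P(Z > 1.96 − bias/0.269): 5.6% at 0.10 SD and 11.2% at 0.20 SD, against 2.5% nominal.

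**6. Precision.** The detectable difference at 80% power is (1.960 + 0.842) × √(2/n): 0.67 SD at n = 35 per arm, 0.75 at 28, 0.81 at 24 and 0.87 at 21 (20%, 30% and 40% loss, assumed). This is an upper limit on the cost of the rules, since some leavers would decline assessment anyway.

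**The case against.** The strongest reply is that the plan already protects itself. Earlier data are retained and a mixed model uses them, so stoppers contribute every visit up to stopping. If stopping depends only on scores already recorded, the bias is at most 0.01 SD. This stands. A reader might infer that the trial becomes a completers-only comparison; the documents do not support that.

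Second, the imbalance between arms is inferred. The text does not say that dropping the psychological sessions while keeping food aid counts as leaving the programme, and the adherence interviews suggest that partial adherers are still seen. This also stands, so the arm mechanism is conditional. Nor is the direction settled: controls have no scheduled psychological support, so rules triggered by deterioration could remove more of them.

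Third, the psychiatric route bears most directly on the secondary outcomes. That is fair for that criterion. A social emergency, or leaving food aid, can plausibly bear on food insecurity itself.

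Two further readings are tempting and should not be pressed:
- One could read "being currently engaged in a structured psychological intervention protocol" as describing the experimental arm itself. In Table 1 it is paired with prior participation in a similar study, and the natural meaning is some other intervention. This is not a contradiction.
- One could read referral as triggering the stop. Referral is for an evaluation; the criterion concerns regular specialised treatment. A further step is needed.

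Finally, calling someone lost to follow-up is a classification, not an explicit bar on assessment. But no other text shown says that assessments continue.

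**Conclusion.** The concern holds as a risk created by the stated rules. As written, the plan produces avoidable missing outcomes after randomisation, and the planned analyses protect against only part of what could follow. Under assumed unequal stopping with unrecorded worsening, the bias is about 0.10 to 0.20 SD. It is about zero if stopping depends only on observed scores, or if it is equal with the same mechanism in both arms. It changes sign if more controls stop, or if people stop because they improved.

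A reader might infer that the comparison is certainly biased in favour of the combined arm. The documents do not support that: they give no dropout rates, so neither size nor direction can be fixed. The error rates of 5.6% to 11.2% belong to one chosen scenario and are not a forecast. What is firm is that the passages do not agree on who is assessed after leaving the programme, and that outcomes not collected cannot be recovered at analysis.

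**What to change.** - State that every randomised participant is invited to T1, T2 and T3 and analysed in the allocated arm, whether or not they still use food aid or psychological support, unless they withdraw consent for data or can no longer validly consent.
- Restrict loss to follow-up to people who cannot be reached or who decline assessments.
- Say whether leaving one component counts as leaving the programme.
- Record programme discontinuation and new psychiatric care, with dates, as intercurrent events.
- Reconcile the sentence that stops participation with the referral paragraph and the adherence interviews, stating whether it ends the support, the outcome assessments or both. Decisions about support and safety stay with the investigators. A blanket statement that exclusion criteria apply at entry only would not do, because those criteria include inability to give informed consent.

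The cost is protocol and information-sheet wording and some extra assessment contacts with people who have left the programme. No additional participants are needed.

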## Discussion

The objective of this study is to better understand the issues related to FI among precarious young adults and its associations with ACE, trauma and psychological distress. The aim is to adapt support systems in MLs services and to expand access to care. By focusing on a population facing multiple and cumulative forms of vulnerability, this research seeks to contribute to a more integrated and clinically relevant understanding of the links between material deprivation, trauma, and mental health. The results are expected to inform both scientific knowledge and professional practices by modeling the interrelationships between FI, ACEs, and psychological symptoms, while supporting the development of accessible and appropriate care pathways within these institutions.

We expect the results to highlight a significant prevalence of ACEs, trauma-related symptoms, and psychological distress among young people experiencing FI. We hypothesize that FI is not merely a contextual or socioeconomic correlate of psychological distress, but may constitute a central clinical determinant that interacts with earlier traumatic experiences. From this perspective, FI may reflect disruptions in the regulation of basic needs rooted in childhood adversity. This deregulation appears to be a determining factor in mental health.

Previous studies have demonstrated the impact of traumatic experiences on the development and persistence of FI, as well as their combined impact on psychological suffering. These findings underscore the importance of considering FI as a chronic stressor that exacerbates psychological suffering, rather than as a secondary or peripheral issue [59, 60]. Furthermore, FI is not always an individual problem. When a family is affected, the consequences impact both parents and children [61, 62]. In line with this literature, our study emphasizes the need to place basic needs at the heart of mental health care, as psychological interventions are likely to be limited in their effectiveness when conducted in contexts of ongoing material deprivation. Addressing FI may therefore represent a necessary, though not sufficient, condition for psychological stabilization and recovery [63, 64].

A central contribution of this research lies in its multidimensional and mixed-methods design. The planned network analyses may help clarify the role of FI within complex symptom systems [54]. This approach allows for a nuanced understanding of how material and psychological factors interact dynamically, in line with lived experience. By identifying central and bridging elements within symptom networks, this perspective may help clarify how material conditions and psychological processes interact and mutually influence one another over time [65].

In parallel, the qualitative and exploratory dimensions of the study are expected to provide insight into how FI and psychological suffering are perceived, interpreted, and managed in everyday professional practice within ML services. Given the heterogeneity of practices and institutional constraints across these structures, this exploratory approach is essential to understanding how young people’s suffering is perceived and addressed in everyday clinical work. These findings are expected to highlight gaps between identified needs and available responses, as well as tensions between social support, emergency aid, and psychological care, thereby informing future adaptations of support systems [66].

Finally, the longitudinal comparative intervention study aims to assess the respective and combined effects of food assistance and psychological support. We expect that while food aid alone may lead to short-term improvements in distress, the combination of food security and sustained psychological follow-up will result in greater and more durable reductions in psychological symptoms, particularly those related to trauma. This study may also shed light on differential trajectories according to the type of ACE, suggesting the need for more tailored, trauma-informed interventions [67]. We think that trauma-focused care could generate significant improvements, in addition to meeting unmet needs [68].

Ultimately, this research project aims to support the development of comprehensive, evidence-based prevention and intervention strategies that acknowledge the inseparability of material conditions and mental health. By positioning food insecurity as a central clinical and public health issue, MISAPSY seeks to promote more holistic, equitable, and transferable models of care for vulnerable young adults within MLs’ services.

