## Method/design

This research project is designed around three distinct methodological approaches. These phases are complementary (see: Table 1).

A cross-sectional study (study 1) based on a quantitative approach, consisting of the widespread distribution of standardized online questionnaires and scales (see: Measures) to young adults receiving support from any ML nationwide.The instruments facilitate a systematic collection of quantitative data and a multidimensional analytical framework to model the associations between psychological and social vulnerability factors. This design supports the identification of overarching statistical patterns.A qualitative study (study 2) intended for psychologists within MLs. This exploratory study offers a complementary perspective on understanding the experiences of youth at the MLs. By collecting data through verbatim analysis this study helps to identify some of the individual and institutional issues that influence the dynamics of care in these structures.An interventional longitudinal study (study 3) comparing two support programs. It is a multicenter, two-arm, parallel-group, single-blind randomized controlled trial. Participation is voluntary for young people experiencing severe FI and psychological distress, with a history of ACE, exclusively from MLP. The control group receives weekly food assistance for 12 months. The experimental group benefits from an intervention combining weekly food assistance for 12 months and twice-monthly psychological follow-up for 6 months. The study follows a superiority framework, hypothesizing that the combined intervention (food assistance plus psychological support) will lead to greater improvements in psychological distress and FI level compared to food assistance alone.

*Participants are assessed 4 times (T0: start of the program*,* T1: 3 months after the beginning*,* T2: end of the psychological intervention (6 months after the beginning)*,* T3: end of the program (12 months after the beginning). Each assessment period allows for the measurement of changes over time through standardized scales and semi-structured qualitative interviews. Detailed analyses will enable comparison of the specific effects of each intervention.*

**Table 1 Tab1:** Summary table of the research methodology

	Study 1	Study 2	Study 3

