### Data analysis

#### Study 1

The statistical analyses of the cross-sectional study will be performed using R software (RStudio), applying a significance level of 0.05. Descriptive and multivariate analyses (e.g., Chi-square/Fisher’s exact tests, correlation tests, ANOVA, etc.) will be used to characterize the population. The research team will also conduct correlation and factor analyses. In addition, we intend to perform a network analysis [54]. We will refer to the STROBE guidelines for epidemiological studies [55].

### Study 2

The analysis of the data from the semi-structured interviews will be conducted following a CQR approach. The themes will be identified by two researchers, using a structured and iterative procedure, aimed at the systematic search for a consensus among researchers. A third researcher, external to the data analysis, will be responsible for validating the categories in order to minimize primary group biases. The process will follow COREQ-32 recommendations [56, 57]. NVivo 15 software will be used.

### Study 3

The primary analysis will be based on repeated-effects linear mixed models, allowing assessment of the evolution of scores over time while taking into account intra-individual correlation and the longitudinal structure of the data. The group x time interaction, defined a priori, will be tested with a two-sided significance threshold set at α = 0.05, without correction for multiple comparisons. In addition, the research team will conduct: intergroup comparisons at several times (Student’s t-tests), intra-group comparison between two time points (paired t-test), exploratory analyses of subgroups based on sociodemographic or biographical variables. If data distribution is non-parametric, analyses such as Mann-Whitney, Wilcoxon, and Kruskal-Wallis tests will be employed. To limit the risk of type I errors in secondary and post-hoc analyses, a significance threshold adjustment will be applied in cases of multiple comparisons, using a Bonferroni correction (corrected α = 0.05 / m, where m corresponds to the number of tests performed within the same set of hypotheses). Exploratory analyses will be clearly identified as such and interpreted with caution, given the sample size.

Missing data will be taken into account based on their nature and frequency. If their proportion exceeds 5%, multiple imputation may be considered to limit bias, subject to the identified non-response mechanism [58].

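### Study 3 is said to assess food aid and psychological support separately and together, but both arms get the same food aid, so only the added effect of psychological support is identified

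*Protocol article*

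**What the plan says.** - **Aim.** The Discussion states that "the longitudinal comparative intervention study aims to assess the respective and combined effects of food assistance and psychological support". It adds: "We expect that while food aid alone may lead to short-term improvements in distress". Method/design closes its description of Study 3 with: "Detailed analyses will enable comparison of the specific effects of each intervention".
- **Design.** Method/design: "It is a multicenter, two-arm, parallel-group, single-blind randomized controlled trial". Procedures, Study 3, on the comparator: "The control group will receive food assistance once a week for 12 months". On the other arm: "The experimental group will receive the same food aid and in addition, psychological support twice a month for 6 months".
- **Entry and outcomes.** Table 1 requires "PHQ-9 score > 15 GAD-7 score > 10", a positive answer to FIES item 8 and at least one ACE. Procedures makes change in food insecurity from T0 to T3 the primary outcome. Changes in PHQ-9 and GAD-7 are among the secondary outcomes.
- **Analysis.** Data analysis, Study 3, makes the group-by-time interaction in a linear mixed model the primary test. Among the additional analyses it lists "intra-group comparison between two time points (paired t-test". The Methods part of the Abstract names pre/post comparisons first among the ways intervention effects will be examined.
- **Timing.** Procedures has eligibility checked at an interview, then 15 days for reflection and consent. Participants complete the scales at each of T0 to T3. The article does not say whether the T0 scores are new or are the screening scores.

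**The concern.** An effect of food aid can be estimated without further assumptions only if some randomised participants do not receive it, and here all do. The only material bearing on food aid is uncontrolled change over time, and the article gives that change a role in examining intervention effects. It also says in advance that it expects food aid alone to improve distress for a time.

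A significant fall in the control arm could then be reported as a benefit of food aid when other causes would produce the same fall. One of these is built into the design: participants are selected for high values on scales that are then followed as outcomes. Since the project wants to inform models of care for Mission Locale services, an unsupported statement on food aid could become one of its main messages.

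**Working it through.** **1. What randomisation identifies.** Let F be food aid and P psychological support, and write Y(F,P) for the mean outcome.

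- Control arm: Y(1,0). Experimental arm: Y(1,1).
- Between-arm contrast: Y(1,1) − Y(1,0), the effect of P given F. Identified.
- Effect of food aid: Y(1,0) − Y(0,0). Combined effect: Y(1,1) − Y(0,0). No arm supplies Y(0,0), so neither is identified.

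The Discussion's aim therefore fails for food aid and for the combination against neither. It does not fail for psychological support.

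**2. What within-arm change contains.** Change from T0 in the control arm is any food-aid effect plus natural course, other Mission Locale support, repeated scales and interviews, and any regression to the mean. Two statements add to the mixture. Procedures says the services already exist and are being reorganised for the study, so T0 need not be free of food aid. Safety considerations allows referral to the Mission Locale psychologists in either group. The mixed model's time terms carry the same mixture as the paired tests.

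**3. How large regression to the mean could be.** The plan has no figure to reproduce here: Study 3 states no effect size, SD or power, and 2 × 35 = 70 is its whole sample-size statement.

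Inputs from the article: entry at PHQ-9 above 15; 35 per arm; two-sided 0.05. Assumptions, not in the article: source PHQ-9 mean μ of 10 or 12, SD 6, scores rounded and limited to 0-27, test-retest correlation r from 0.6 to 0.95, no effect and no trend.

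With screening scores as T0, the expected fall is (1 − r) × (mean of those selected − μ). The mean of those selected is about 18.75 for μ = 10 and 19.19 for μ = 12. Simulation of 2,000,000 persons per setting gives:

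| μ | r | Fall by formula | Simulated fall | SD of change | Fall / (SD/√35) | Paired test significant |
|---|---|---|---|---|---|---|
| 10 | 0.6 | 0.40 × 8.75 = 3.50 | 3.53 | 4.88 | 4.28 | 99% |
| 10 | 0.7 | 0.30 × 8.75 = 2.63 | 2.64 | 4.33 | 3.61 | 94% |
| 12 | 0.8 | 0.20 × 7.19 = 1.44 | 1.46 | 3.60 | 2.40 | 65% |
| 10 | 0.95 | 0.05 × 8.75 = 0.44 | 0.46 | 1.90 | 1.43 | 28% |
| 12 | 0.95 | 0.05 × 7.19 = 0.36 | 0.38 | 1.90 | 1.18 | 21% |

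With a fresh T0 and the same correlation between any two occasions, the whole expected fall comes before T0. For μ = 10 and r = 0.7 the mean goes from 18.75 at screening to 16.10 at T0 and then stays level. The paired test is significant in about 5%. If correlation weakens as the interval lengthens, some fall remains after T0.

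The between-arm test on change stays at about 5% in all these settings.

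**4. Wider assumptions.**

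- Selecting on PHQ-9 and GAD-7 jointly, with source PHQ-9 mean 8 to 13 and r from 0.7 to 0.95, gives 19-99% with screening scores as T0. At an assumed Bonferroni level of 0.05/3 it is still 9-97%: the problem is bias, not multiplicity.
- For the primary scale, a Rasch-type simulation of FIES with assumed item severities, r from 0.5 to 0.95 and selection on item 8 gives falls of about 0.5 to 1.7 points and 50-97% significant. The between-arm test lies at about 4-7%.

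**The case against.** The statements that govern the trial are already framed correctly. The fourth objective in the Background compares two support systems. Method/design sets a superiority hypothesis of the combination against food aid alone. The primary test is the randomised group-by-time interaction. The sentence in Method/design on specific effects can fairly be read as comparing the two programmes between arms. The paired tests come after the primary model, and the expectation about food aid is hedged. The lack of an arm without food aid is explained on ethical grounds. All of this stands, and it limits the problem to the stated aim and the supplementary analyses.

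A reader might go further and infer that regression to the mean will appear as a food-aid effect. The article does not support that. Eligibility is checked before the reflection period and scales are completed at T0, which leans towards a new measurement without saying so. With one, the artefact may largely disappear. A reader might also infer that significance in one arm only will be taken as a difference between arms, or that a paired test is meant to prove a food-aid effect. No passage says either.

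What survives is the mismatch between aim and design. It does not depend on regression to the mean: even with a fresh T0, natural course, other support and repeated assessment remain mixed with food aid.

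**Conclusion.** The point holds, as something that should be fixed rather than a flaw in the primary result. Confidence is high that Study 3 identifies only the added effect of psychological support given food aid, since this follows from the two arms as described.

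The size of any regression to the mean is uncertain. The false-significance rate of a within-arm PHQ-9 test runs from about 5% to about 99%, depending mainly on whether screening scores are reused as T0 and on the test-retest correlation. The article gives neither, nor the source distribution. The primary group-by-time analysis is not biased by this, and the sample size is untouched.

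**What to change.** - **Discussion:** restate the aim of Study 3 as estimating the added effect of psychological support among participants who all receive food aid.
- **Method/design:** make clear that the sentence on specific effects means a between-arm comparison of the two programmes.
- **Abstract and Data analysis:** rest every statement of effect on the between-arm contrast. Report within-arm change, whether paired or from the mixed model's time terms, descriptively with confidence intervals and a note that it cannot be attributed to food aid. Dropping the paired t-tests alone would not be enough, because the model yields the same change.
- **Procedures:** use T0 scores measured separately from the screening scores, or state that the screening scores are reused.

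The cost is wording and a few tests, plus one further completion of the scales if T0 would otherwise reuse the screening scores. The trial gives up inferential within-arm tests and a causal statement on food aid that its design cannot support. Arms, recruitment and the primary analysis stay as they are.
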